#### Secondary outcomes

The Beck Depression Inventory-Second Edition (BDI-II) [52] is included as another depression outcome measure. The Beck Anxiety Inventory (BAI) [53] was added to the protocol through an administrative supplement to the parent project to determine whether treatment effects generalize to anxiety. The following assess functional outcomes: Quality of Life Enjoyment and Satisfaction Questionnaire (Q-LES-Q) [60], Sheehan Disability Scale (SDS) [61], and the MOS SF-20 [64].

### Participant timeline {13}

The participant timeline is shown in Fig. 2.

**Fig. 2 Fig2:**
[figure not shown]
Schedule of enrollment, interventions, and assessments

### Sample size {14}

With a target *N* = 160 (80 subjects in each of the two treatments), the study will have 80% power to detect main effect differences of 22% (e.g., 28% vs. 50%) in winter 2 recurrence, which we expect at a naturalistic follow-up [14, 44]. Sample sizes for comparisons of winter 3 recurrence will depend on the number of recurrences at winter 2. Based on the recurrence rates observed in our prior study, we project that there will be about 37 recurrences in the LT group and 22 recurrences in the CBT-SAD group. This will provide 80% power to detect a difference in winter 3 recurrence of 35% (e.g., 60% vs. 25%) between CBT-SAD➔LT and LT➔CBT-SAD and a difference of 27% (e.g., 23% vs. 50%) between CBT-SAD and LT subjects without winter 2 recurrence. For biomarker comparisons, there will be 80% power to detect differences of 0.45 standard deviation (SD) in post-treatment values or in pre-post treatment changes between CBT-SAD and LT. Power for detecting relationships between biomarkers and outcomes were based on the odds ratio associated with an increase of 1 SD in the biomarker value or its change. For post-treatment remission, there will be 80% power to detect an OR of 2.2 in the CBT-SAD or LT group and a 2.4-fold difference in the ORs for the two treatments. For winter 2 recurrence, there will be 80% power to detect an OR of 2.2 in the LT group, an OR of 2.8 in the CBT-SAD group, and a 2.9-fold difference in their ORs. There was minimal attrition (4.5%) in our previous study, and we anticipate similar retention in this study. However, with attrition as high as 20%, there will be 80% power to detect a difference in winter 2 recurrence of 24% between CBT-SAD and LT and a difference of 39% in winter 3 recurrence between the two switch groups. Empirical sample size estimates^21^ indicate that the study will have at least 80% power to detect a mediated effect if the regression coefficient for the direct effect of treatment after adjustment for the mediator is at least .39 and the coefficients for the effect of treatment on the mediator and the effect of the mediator on outcome after adjustment for treatment are at least .26.

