## Abstract

**Background:**

This study is a confirmatory efficacy trial of two treatments for winter seasonal affective disorder (SAD): SAD-tailored group cognitive-behavioral therapy (CBT-SAD) and light therapy (LT). In our previous efficacy trial, post-treatment outcomes for CBT-SAD and LT were very similar, but CBT-SAD was associated with fewer depression recurrences two winters later than LT (27.3% in CBT-SAD vs. 45.6% in LT). CBT-SAD engaged and altered a specific mechanism of action, seasonal beliefs, which mediated CBT-SAD’s acute antidepressant effects and CBT-SAD’s enduring benefit over LT. Seasonal beliefs are theoretically distinct from LT’s assumed target and mechanism: correction of circadian phase. This study applies the experimental therapeutics approach to determine how each treatment works when it is effective and to identify the best candidates for each. Biomarkers of LT’s target and effect include circadian phase angle difference and the post-illumination pupil response. Biomarkers of CBT-SAD’s target and effect include decreased pupillary and sustained frontal gamma-band EEG responses to seasonal words, which are hypothesized as biomarkers of seasonal beliefs, reflecting less engagement with seasonal stimuli following CBT-SAD. In addition to determining change mechanisms, this study tests the efficacy of a “switch” decision rule upon recurrence to inform clinical decision-making in practice.

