This confirmatory efficacy R01 trial focuses on two non-pharmacological treatments that each work for some SAD patients: light therapy (LT; i.e., daily exposure to bright artificial light during the symptomatic months), and SAD-tailored group cognitive-behavioral therapy (CBT-SAD) [11]. Substantial evidence supports LT as an efficacious acute SAD treatment [12]. In our previously completed R01-level efficacy trial enrolling 177 adults with SAD, CBT-SAD and LT were very similar in terms of symptom improvement and the proportions in remission at post-treatment (47.6% CBT-SAD, 47.2% LT) [13]. However, two winters later, CBT-SAD was associated with significantly fewer depression recurrences (27.3% CBT-SAD, 45.6% LT) and lower depression severity than LT [14]. These findings suggest that slightly more than one-quarter of those treated with CBT-SAD and slightly less than half of those treated with LT have a depression recurrence, highlighting the need for reliable strategies for precision medicine in clinical practice. In the current project, we apply the experimental therapeutics approach to determine how each treatment works and to identify the best candidates for each. Consistent with the NIMH’s focus on biological endpoints, we will ascertain whether theoretically derived candidate biomarkers of each treatment’s target and effect are prescriptive of better outcomes in that treatment vs. the other.

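### The 80% power for the primary comparison assumes a 22-point difference, but the same paragraph projects 22 vs 37 recurrences (18.75 points), where power is about 70%

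*Protocol article*

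**What the plan says.** All the statements at issue are about winter 2 recurrence, the primary outcome. Except for the prior rates, they stand in one paragraph, Sample size {14}.

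- **Size:** 160 participants, "80 subjects in each of the two treatments".
- **Primary power:** "the study will have 80% power to detect main effect differences of 22% (e.g., 28% vs. 50%) in winter 2 recurrence, which we expect". Two earlier studies are cited for this expectation.
- **Projection for winter 3:** "we project that there will be about 37 recurrences in the LT group and 22 recurrences in the CBT-SAD group". The article attributes these counts to the rates seen in the earlier trial, and the winter 3 power statements for switched and non-recurrent participants are built on them.
- **Attrition:** "There was minimal attrition (4.5%) in our previous study, and we anticipate similar retention in this study". As a worst case, "with attrition as high as 20%, there will be 80% power to detect a difference in winter 2 recurrence of 24" percentage points.

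The prior rates appear in the abstract ("27.3% in CBT-SAD vs. 45.6% in LT") and again in Background and rationale {6a}. Both places describe them as measured two winters after treatment.

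**The concern.** The paragraph gives two different answers to the question of how large a winter 2 difference the trial expects. The primary power statement expects 22 points, illustrated by 28% vs 50%, which is about 22 vs 40 events among 80 per arm. The winter 3 projection expects 22 vs 37 events. The CBT-SAD rate is nearly the same in both (28% and 27.5%); the LT rate is not (50% and 46.25%). Only the higher LT rate gives the advertised 80%.

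Objectives {7} sets out to confirm superiority of CBT-SAD, and the trial is labelled confirmatory. A reader will take 80% as the power for the effect the investigators expect and will weigh a non-significant result accordingly. If power at their own projection is nearer 70%, a null result is weaker evidence against superiority than the paragraph suggests.

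**Working it through.** **Inputs.** From Sample size {14}: n = 80 per arm; 28% vs 50%; 22/80 = 27.5% vs 37/80 = 46.25%; attrition 4.5% (80 × 0.955 = 76.4 per arm) or 20% (80 × 0.80 = 64 per arm). Alpha and sidedness are not stated; I assume two-sided 5%, so z = 1.96.

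**Formula** (two proportions, normal approximation, pooled variance under the null, no continuity correction), with d the difference and p̄ the mean rate:

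power = Φ{ [ d − 1.96·√(2p̄(1−p̄)/n) ] / √( [p₁(1−p₁) + p₂(1−p₂)]/n ) }

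The unpooled version, Φ{ d/√([p₁(1−p₁) + p₂(1−p₂)]/n) − 1.96 }, supplies the upper end of each range.

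**Step 1: reproduce the stated figure.** 28% vs 50%, n = 80: d = 0.22, p̄ = 0.39.
- Null SE = √(2 × 0.39 × 0.61/80) = 0.0771; × 1.96 = 0.1512.
- Alternative SE = √((0.2016 + 0.2500)/80) = 0.0751.
- Power = Φ((0.22 − 0.1512)/0.0751) = Φ(0.916) = 82.0% (unpooled 83.4%; exact enumeration of the chi-square test 81.6%).
- With 4.5% attrition, pooled power is 80.2%.

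The stated 80% is sound for these rates.

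**Step 2: check the alpha assumption.** At 64 per arm, a 24-point difference gives 79.9% (28% vs 52%) or 80.6% (26% vs 50%), matching the article's claim for 20% attrition. One-sided 5% would give 89.3% at 28% vs 50% with 80 per arm, which does not match. Two-sided 5% without continuity correction fits both stated figures.

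**Step 3: power at the projected counts.** 27.5% vs 46.25%, n = 80: d = 0.1875, p̄ = 0.36875.
- Null SE = √(2 × 0.36875 × 0.63125/80) = 0.0763; × 1.96 = 0.1495.
- Alternative SE = √((0.1994 + 0.2486)/80) = 0.0748.
- Power = Φ((0.1875 − 0.1495)/0.0748) = Φ(0.508) = 69.4% (unpooled 70.7%; exact 69.5%).

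**Step 4: the same rates with attrition, and the unrounded prior rates.**

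| Rates | n per arm | Power (pooled / unpooled) |
|---|---|---|
| 28% vs 50% | 80 | 82.0% / 83.4% |
| 27.5% vs 46.25% | 80 | 69.4% / 70.7% |
| 27.5% vs 46.25% | 76.4 | 67.4% / 68.7% |
| 27.5% vs 46.25% | 64 | 59.6% / 61.1% |
| 27.3% vs 45.6% | 80 | 67.5% / 68.8% |

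The projection follows the prior rates: 80 × 0.273 = 21.8 and 80 × 0.456 = 36.5.

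**Step 5: how far the projection falls short.** With 80 per arm, the smallest difference reaching 80% power is about 21 to 21.5 points, against 18.75 projected. For 80% power at the projected rates:

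n = [1.96·√0.4655 + 0.8416·√0.4480]² / 0.1875² = 1.9006²/0.03516 ≈ 103 per arm.

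**Step 6: does the plan rely on the projection?** Yes. It leaves 80 − 22 = 58 and 80 − 37 = 43 participants without recurrence, and at 23% vs 50% these give 81% power, in line with the 80% stated for that winter 3 comparison.

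**The case against.** The best defence has four parts.

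1. **No sum is wrong.** The article says 80 per arm detects 22 points with 80% power, and it does. This stands: the problem is conflicting inputs, not a miscalculation.
2. **28% vs 50% is only an example of a detectable difference.** True, but the sentence says the 22-point difference itself is expected, and the projection implies 18.75.
3. **The two figures have different bases.** The expectation cites two studies; the projection cites one. Explanation for the choice of comparators {6b} says the second study measured recurrence the next winter, the same time point as winter 2, whereas 27.3% and 45.6% were measured two winters later. A pooled expectation could differ legitimately. But the article gives no rates from the second study and does not use it to explain the gap. For this reason the result at 27.3% vs 45.6% is secondary; the conflict lies between two winter 2 statements and does not depend on it.
4. **The projection is approximate and serves only winter 3.** The gap is about three LT patients (37 vs 40), and winter 3 power barely changes with either count. That is fair for winter 3. For the primary comparison, the same three patients move power from about 82% to about 69%.

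It is also fair to say that nothing in the article announces that a null result will be read as no difference. The risk of over-reading is a judgement about readers.

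**Conclusion.** The concern holds. Sample size {14} carries two incompatible expectations for the primary endpoint, and the 80% belongs only to the larger. At the article's own projected counts, power is 69–71% with 80 per arm, 67–69% with the anticipated attrition and 60–61% with 20% attrition. The type II error at the projection is about 30% rather than 20%.

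These figures assume a two-sided 5% test without continuity correction, the variant that fits the article's other power claims. With a continuity correction they would be lower: 77.3% at 28% vs 50% and 63.3% at the projected counts, both with 80 per arm. One-sided 5% would give 79.6% at the projected counts but would contradict the stated 80% at 28% vs 50%. The finding does not show which set of rates is the better forecast, only that the paragraph cannot use both.

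**What to change.** Use one set of winter 2 rates throughout Sample size {14}.

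- If the prior study's rates are the expectation, state the primary power at 22 vs 37 events of 80: about 70%, and about 60% with 20% attrition. Keep 22 points as the difference detectable with 80% power, and stop calling it expected.
- If 22 points really is the expectation, give the rates from the second cited study that support it, and base the winter 3 group sizes on the same rates.
- In either case, state alpha and sidedness.

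A useful companion sentence would say that a non-significant primary result will be interpreted from the confidence interval for the risk difference, not as absence of superiority.

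The cost is wording and a less favourable power figure. Trial status has recruitment ending in February 2022, so the 103 per arm above measures the shortfall; it is not a request to enrol more participants.

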### Recruitment {15}

We intend to draw our sample from the combination of a multi-media advertising campaign and referrals from local health and mental health clinics beginning in September and continuing through early January of each year of recruitment. These recruitment strategies mirror those previously implemented by the P.I. to recruit cohorts of 40–50 new cases/year in prior studies. Our last study included 177 subjects recruited over 6 years; however, the first 2 years enrolled 24 subjects under an intramural pilot grant. The remaining 153 subjects were recruited under the R01 in 4 cohorts: 24, 33, 50, and 46. This averages 38 subjects/year, but we intentionally kept recruitment low the first two R01 years while we hired staff. While we had hoped to recruit cohorts of 50–55/year and complete recruitment in project years 1–3 for the current project, it proved difficult to recruit cohorts of that size, especially during the COVID-19 pandemic, and we extended recruitment into project year 4. Completion of all follow-ups through winter 3 will be possible with a one-year no-cost extension.

Our advertising campaign targets the major area newspaper, free local/community papers, neighborhood email list serves, Facebook, and radio advertisements across stations that cater to different demographics. To generate referrals, the P.I.’s laboratory maintains an updated database of all > 500 physicians (including all specialties), > 60 licensed Doctoral and Master’s-level psychologists, and > 20 private practice groups and community mental health centers in Chittenden County, the county where Burlington is located. Each September, we will perform outreach through these various sources and invite referral of SAD patients. We have found that these sites recognize our specific expertise in SAD (i.e., expertise they do not tend to have) and are glad to refer these cases for SAD-specific services through our research. Burlington, VT is home to the University of Vermont Larner College of Medicine, the largest employer of physicians in the State. Most Vermont residents centralize their healthcare needs in Burlington and are used to coming to Burlington for their healthcare. Therefore, we routinely do outreach to colleagues in the Medical School to generate referrals each year.

The rate of participant accrual is tallied, including a breakdown of rates for women and ethnic minorities, at the conclusion of each recruitment period (i.e., in the winter), and will be formally reviewed each study year by the P.I. and the DSM Board, and (at annual IRB review of the project) by the University of Vermont IRB. The number of participants who consented but did not qualify (i.e., were screened out at the medical screen or did not develop a SAD episode) and the number of qualified, enrolled participants who dropped out will also be analyzed to detect patterns of insufficient recruitment rates. These will be addressed aggressively with modified recruitment strategies so that we can meet our recruitment goals.

## Assignment of interventions: allocation

### Sequence generation {16a}

Participants will be randomly allocated to one of the two equal-probability conditions on a continuous basis as they qualify. Project biostatistician/co-investigator (P.M.V.) will design the schedule based on permuted random-size blocks of 4 and 8, stratified by three variables: [1] sex at birth, [2] comorbid diagnosis with two levels (present/absent), and [3] antidepressant medication status with two levels (on medication or not).

### Concealment mechanism {16b}

Only the project statistician will have access to the schedule and will prepare numbered, sealed envelopes with treatment assignments for each stratum.

### Implementation {16c}

Only the project coordinator, who will not conduct outcome assessments, will sequentially open the envelopes as subjects enroll to determine treatment group. Both the project statistician and an independent statistician will routinely check implementation of the randomization for accuracy.

## Assignment of interventions: blinding

### Who will be blinded {17a}

All study personnel other than the PI, the project coordinator, the project biostatistician, and CBT-SAD group facilitators will be masked to study treatment. Importantly, the trained research assistants who administer the primary outcome measure, the SIGH-SAD, will be blinded. Before each SIGH-SAD administration, the rater will inform the participant to answer the questions about symptoms over the past week without disclosing their treatment assignment. If a participant reveals their treatment assignment during a SIGH-SAD, the interview continues, but the rater marks the interview as unblinded and notes the time during the audio-recording when unblinding occurred. The project coordinator then erases the part of the interview when unblinding occurs, assigns a new (blinded) rater to rate the interview in place of the original interviewer, and avoids scheduling the participant with an unblended rater at future time points. Procedures for maintaining the blind in data management are discussed under the Data Management Plan, below.

### Procedure for unblinding if needed {17b}

The authors do not anticipate a requirement for unblinding because participants are aware of their treatment assignment. In the event of adverse events, the Principal Investigator is also aware of participant treatment assignments.

## Data collection and management

### Plans for assessment and collection of outcomes {18a}

#### Biomarker assessments

Pupillary and EEG data will be collected at pre-, mid-, and post-treatment in winter 1; at winter 2 follow-up (and for those who recur and are switched to the alternate treatment modality, again at mid- and post-treatment in winter 2); and at winter 3 follow-up (for all subjects, regardless of recurrence or switch status). The schedule for PAD is the same, with the exception of mid-treatment, due to subject burden and DLMO expense.

##### PIPR

The PIPR will be assessed using previously validated methods in SAD [26, 31]. The PIPR metric is calculated as the difference between pupil responses to red and blue light, as only responses to blue light reflect the circadian system. Due to daily variation in retinal responsivity, participants will undergo PIPR testing only during the daily plateau in responsivity. Stimuli are electronically controlled via light emitting diodes within the DP2000 Neuroptics (Irvine, CA) pupilometer goggles. Stimuli are 22.68 nm full width half-maximum (FWHM; 467.7 nm blue light) and 15.78 nm FWHM (632.9 nm red light) and both are calculated to yield a retinal irradiance of 13.5 log photons/cm^2^/s as measured radiometrically (USB4000 Spectrometer, OceanOptics, Dunedin, FL). Calculated retinal irradiance accounts for age-related lens density and the difference in transmission of red and blue wavelengths through the lens [65]. We will use lights of equal retinal irradiance (13.5 log photons/cm^2^/s) stimuli of 200 ms based on Park et al. [66]. The red and blue exposures will be alternated four times each. Our irradiance is comparable to Gamlin et al. [30] (13.5–14.1 log photons/cm^2^/s) and Zele et al. [67] (14.2 log photons/cm^2^/s). Pre-processing via MATLAB (Natick, MA) for the PIPR includes [1] blink removal, [2] averaging the pupil area, and [3] calculating Net PIPR. Linear interpolation is used to define and replace blink data points using co-investigator’s (K.A.R.) laboratory’s standard methodology [31]. The PIPR will be analyzed for 30 seconds, beginning 10s after light OFF, and both blue and red PIPR will be calculated as a percentage of baseline constriction 7 s prior to stimulus onset. We use an 11 min dark adaptation period just prior to testing, and 45 min in dim light prior to that (< 50 lux). We are using 2 min intervals between stimuli to reduce potential cumulative effect of repeated stimuli. We average all four trials for red and blue, regressed on calculated retinal irradiance for each trial, and then calculate a Net PIPR (blue–red). One of the benefits of the Net PIPR is that drug effects are expected to affect the PIPR response to both blue and red light similarly. The main difference between the red and blue PIPRs is that the blue PIPR includes responses due to intrinsically photosensitive retinal ganglion cells (ipRGCs), while the red does not. Subtracting the red response from the blue leads to a Net PIPR value excluding all influences on pupil dilation except the ipRGC effect. Therefore, effects on pupil dilation of caffeine, nicotine, antidepressant medications, alcohol, exercise, diet, or even autonomic regulation, as examples, in SAD will be controlled mathematically with Net PIPR.

##### Wrist actigraphy

Participants will wear the motion-sensitive ActiGraph GT3XP-BLTE (Pensacola, FL) on their non-dominant wrist for 24-h a day for one week. Actigraphs record the number of movements per unit time, and analysis of these data will provide an objective measure of sleep/wake patterns not subject to recall bias like self-report. Wake time, based on actigraphy, will be entered as a covariate in analyses with the PIPR to control for time since wake and diurnal variation.

##### Pittsburgh Sleep Diary (PghSD)

Concurrent with the actigraphy for one week, participants will complete the PghSD [54], a diary of sleep-wake behavior, via a secured internet website that tracks time of completion to ascertain that the data is truly prospectively collected, rather than sporadically and retrospectively completed. Upon awakening in the morning, questions are as follows: the times at which the participant went to bed and attempted to fall asleep; the number, cause, and duration of nocturnal awakenings; final time out of bed; and total estimated time asleep. Visual analog scales estimate overall sleep quality and mood and alertness upon awakening.

##### Dim light melatonin onset (DLMO)

Estimation of the evening time of DLMO will be conducted at home, following the 1-week actigraphy assessment using salivettes to collect salivary melatonin levels every 30 m from 7 h prior to habitual bedtime until 1 h past habitual bedtime while under dim (< 10 lux) light to prevent acute melatonin suppression by light. Participants will be fitted with dark-colored goggles for 95% light filtration (Uvex Flex Seal with Shade 5.0 Infra Dura lens) to wear for the collection procedure.

